## Abstract

Supplemental Digital Content is available in the text

## Introduction

1

Micronutrient deficiencies are common during pregnancy, especially in pregnant women from economically disadvantaged settings where diets with low content of minerals and vitamins are consumed.^[1]^ Selenium is a non-metallic chemical element of great importance to human health.^[2,3]^ It is a key component of several human seleno-proteins and mostly involved in redox reactions.^[4]^ It acts as an antioxidant and helps protect the body against the damaging effects of free radicals.^[5]^ Selenium is essential for the activity of the enzyme glutathione peroxidase (GPX), a main intracellular antioxidant that protects against reactive oxygen species and subsequent oxidation-induced cellular damage.^[5,6]^ Biochemical selenium deficiency has been associated with increased mortality among those infected with HIV^[7]^ and with accelerated HIV disease progression through increased viral load.^[8]^ Selenium's role in antioxidant defence^[9]^ and immunity^[10]^ may be the underlying mechanism. There is, however, limited data on the selenium status of Nigerian pregnant women with HIV-infection, with a recent study conducted by us showing a prevalence rate of selenium deficiency to be 20.4% and we reported significantly increased rates of preterm birth and delivery low birth weight babies among the HIV infected participants with selenium deficiency.^[11]^ Several other studies have also reported low selenium status in HIV-infected individuals, and that serum selenium concentration declines with disease progression.^[12,13]^

Selenium is found in cereals, meat, poultry, seafood, and eggs.^[6]^ Cereals may provide about 50% of dietary selenium, however data on the selenium content of Nigerian or African foods is also limited. The selenium content of plant foods varies with the selenium content of the soil.^[6]^ The Recommended Dietary Intake of selenium for pregnant women is 60 mg/day^[6]^ and most interventional studies make use of daily doses of up to 200 μg selenium in its elemental form (selenomethionine).^[14–17]^ Supplemental doses up to 200 μg of the mineral should not cause adverse effects, even if temporarily exceeded, since the selenium upper tolerable intake (UL) for this group is established as 400 μg (5.1 μmol) selenium/day.^[18]^ Given the high UL and the regulation of body homeostasis through urinary excretion, selenium supplementation can be regarded as a safe intervention.^[18,19]^ There is still limited data about selenium toxicity in humans, but the most common side effects include: hair and nail brittleness and loss, gastrointestinal disturbances, skin rash, fatigue, irritability and nervous system disturbances.^[6,19]^ Selenium containing supplements are not recommended for children under the age of 15 years.^[6]^ There is currently paucity of studies that examined the effects of selenium supplementation among pregnant HIV-infected black African women. This study will therefore attempt to assess the effect of antenatal selenium supplementation on major pregnancy outcomes (preterm birth and low birth weight) and HIV disease progression rate among pregnant women at the Lagos University Teaching Hospital (LUTH), Lagos, Nigeria.

## Methods and design

2

### Study design and setting

2.1

The study is designed as a prospective, randomized, double-blind, placebo-controlled, single-center trial involving confirmed HIV-seropositive pregnant women who are seeking care at the antenatal clinics of the Lagos University Teaching Hospital (LUTH). LUTH is the teaching hospital of the College of Medicine, University of Lagos. It has more than 1000 beds and is located in the metropolis of Lagos in Southwest Nigeria. The hospital provides services to patients from the neighbouring states in Southwest Nigeria. It is the largest hospital in Lagos State and mainly offers clinical services, including prenatal, intrapartum, and postnatal care. Pregnant women with HIV infections are jointly managed by haematologists and HIV physicians at the hospital's AIDS Prevention Initiative Nigeria (APIN) clinic and undergo regular monitoring of their disease with 3-monthly CD4+ cells count and viral load. Participants’ enrolment will start in September 2018, and the last woman is expected to be included in the trial in February 2019. The Health Research and Ethics Committee of LUTH's Institutional Review Board has granted ethics approval for this study (Approval Number ADM/DCST/HREC/APP/2438; 30th August 2018).

### Study population/ participant enrolment

2.2

Eligible participants are confirmed HIV-seropositive pregnant women aged 15 to 49 years who have a singleton gestation at 14 to 27 weeks’ gestation. The exclusion criteria at enrolment are multiple gestations, significant renal and hepatic impairment, an expected delivery date beyond March 2019, receipt of a long course of mineral supplement containing selenium during the 6 months prior to enrolment, refusal of consent at enrolment or withdrawal of consent during the study.

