### Randomisation and blinding schedule

2.3

Eligible women will be invited to give consent for participation in the trial within 2 weeks of screening. At enrolment, participants will be randomly assigned by a trained research assistant into 2 arms to receive daily oral tablet of 200 μg elemental selenium (arm I) or placebo (arm II) till their delivery using a 1:1 block randomisation code to be generated from Random Allocation software version 1.0 (May 2004) by the study Statistician. The proposed dose of selenium is one-half of the safe and tolerable upper intake level of 400 μg/day for pregnant women.^[18]^ The active drug (selenium) and placebo tablets will be indistinguishable in shape, size, and colour and will be packed in identical coded transparent dispensing sachets by the onsite pharmacy technician who will then store the coded randomization list in a sealed opaque envelope that will be kept in a locked file cabinet at the study site until the end of the study. Twelve (12) dispensing sachets with identical numeric regimen code, containing the same intervention drug will be prepared for each of the participants. At every 2-weekly follow-up visit, a new dispensing sachet with the same numeric code, containing 16 tablets of the same intervention drugs will be given to each woman and pills remaining in used sachets will be counted to assess compliance. In addition, all the women will receive the standard prenatal care (see below). Study investigators and participants will be blinded to the treatment arms until after the final analysis. The onsite pharmacy technician is not involved in the design, conduct, statistical analysis, and reporting of study findings.

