#### Data collection and management

2.5.1

At enrolment, the investigators will collect data on the participants’ socioeconomic status, education, and obstetric history, duration of HIV diagnosis (in months), WHO clinical stage of the disease,^[22]^ type and duration of ART use (in months), baseline Haemoglobin (Hb) levels (in g/dL), CD4 + cells count (in cells/mm^3^) and viral load (in copies/mL), and BMI (actual maternal weight is calculated by subtracting the estimated fetal weight at enrolment using a normogram chart from the measured maternal weight) (in kg/m^2^) using a structured interviewer-administered questionnaire. Gestational age is based on the date of the participant's last menstrual period, which will be obtained at the time of random assignment. Data collection begins on the day a participant is allocated into an intervention arm and continues until the termination of the trial or until the participant withdraws from the trial at any time for any reason. At delivery, data will be collected from the participants’ case notes on the latest CD4 + cells count and viral load (done within the last 6 weeks of delivery), WHO stage of the disease, and latest Hb levels. The total duration of supplement intake – selenium or placebo (in weeks), level of compliance to use of the supplement (good compliance level is defined as usage of at least 10 of the 16, 2-weekly prescribed tablets), mode of delivery, gestational age at delivery (in weeks) and the baby's birth weight (in grams) will also be recorded in the questionnaire. Original data will be transferred to an electronic database system located in a guarded facility at the trial site by the research assistant. Access to the study data is restricted. The PI will have the access to the final dataset. An independent steering committee will monitor and examine strict compliance with the study protocol (Fig. 1 and Table 1). Trial progression or protocol modification will be updated in the registered database (Pan African Clinical Trial Registry, PACTR) and reported to the LUTH's ethical committee that will provide the oversight functions of data and safety monitoring in the course of the study.

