#### Sample size

2.7.1

Using the data from our previous study,^[11]^ we propose to enrol 148 participants in the study to investigate the effect of selenium supplementation on the primary endpoints. The study is powered for a 2-sided test with a Type I error rate of 5% and 95% power, that is, Z_α_ = 1.96 and Z_β_ = 1.64, adjusted for a 20% drop-out rate. We also propose to enrol 180 participants to detect an effect size of 0.3 of selenium supplementation on the major secondary endpoint (reduction in HIV disease progression). This is powered for a 2-sided test with a Type I error rate of 5% and 80% power, that is, Z_α_ = 1.96 and Z_β_ = 1.64, adjusted for a 20% drop-out rate. Therefore, a total sample size of 180 is used in this study with 90 HIV-infected women randomised into each of the trial arms to assess the effects of selenium supplementation on the primary and secondary outcome variables.

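### The due-date exclusion and the 14-to-27-week entry window leave nobody eligible after about 5 January 2019, yet the last inclusion is expected in February 2019

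*Protocol article*

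**What the plan says.** Section 2.2 of the protocol article sets two conditions that together fix the calendar. Participants are women "who have a singleton gestation at 14 to 27 weeks’ gestation", and one of the exclusions is "an expected delivery date beyond March 2019".

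Section 2.1 gives the recruitment period: "Participants’ enrolment will start in September 2018, and the last woman is expected to be included in the trial in February 2019". Section 3.1 (Trial status) repeats the same dates, so February is not an isolated slip.

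Two further statements matter. Section 2.5.1 says "Gestational age is based on the date of the participant's last menstrual period", which ties entry gestation and due date to the same origin. Section 2.7.1 says "a total sample size of 180 is used in this study with 90 HIV-infected women randomised into each of the trial arms". Nothing in the article relaxes the due-date limit or the gestational window for later entrants.

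**The concern.** Gestation at entry and the due date are two views of one quantity, so a fixed calendar limit on the due date also limits the entry date. If that implied date falls before the planned end of enrolment, staff who apply section 2.2 correctly must turn away every woman for the rest of the period. Before that point the lower gestational limit rises week by week, so the criterion in force is no longer 14 to 27 weeks.

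At stake are the feasibility of enrolling 180 women at one centre by the stated date, adherence to the eligibility criteria late in recruitment, and the link between enrolment date and length of supplementation, since treatment runs from entry to delivery.

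**Working it through.** **Inputs**

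- Due-date limit: 31 March 2019, the most generous reading of section 2.2.
- Entry gestation: 14w0d to 27w6d, i.e. 98 to 195 days (section 2.2). A narrower reading stops at 27w0d, 189 days.
- Enrolment: at most 1 September 2018 to 28 February 2019 = 30+31+30+31+31+28 = 181 days (sections 2.1 and 3.1).
- Due date = last menstrual period + 280 days. This is an assumption: the article gives the dating origin but not the term length.

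**Plan's own figure.** The month of last inclusion, February 2019, cannot be reproduced from the section 2.2 criteria.

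**Last possible entry date** = 31 March 2019 − (280 − maximum gestation in days)

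- 27w6d: 280 − 195 = 85 days, giving 5 January 2019.
- 27w0d: 280 − 189 = 91 days, giving 30 December 2018.
- Conversely, a woman entered at 27w6d in February would be due between 27 April (entry 1 February) and 24 May 2019 (entry 28 February).

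**Minimum eligible gestation by entry date** = 280 − (days from entry to 31 March 2019)

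| Entry date | Days to 31 March | Minimum gestation |
|---|---|---|
| 30 Sep 2018 | 182 | 98 d = 14w0d |
| 1 Nov 2018 | 150 | 130 d = 18w4d |
| 1 Dec 2018 | 120 | 160 d = 22w6d |
| 1 Jan 2019 | 89 | 191 d = 27w2d |
| 5 Jan 2019 | 85 | 195 d = 27w6d |
| 1 Feb 2019 | 58 | 222 d = 31w5d |

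The full window is open only to 30 September. From 6 January to 28 February, 26 + 28 = 54 of 181 days (30%), nobody qualifies.

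**Share of the intended pool excluded.** The article gives no accrual pattern, so this part rests on assumptions.

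- Even accrual over all entry days and all 98 gestational days: no loss for the 30 days of September; from 1 October to 5 January the daily loss rises from 1 to 97 gestational days, summing to 97 × 98 / 2 = 4,753; the closed period loses 54 × 98 = 5,292. Total (4,753 + 5,292) / (181 × 98) = 10,045 / 17,738 = 56.6%.
- Counting each pregnancy once by due date: possible due dates run from 25 November 2018 to 29 August 2019, 278 days, of which 151 fall after 31 March. 151 / 278 = 54.3%.
- Other start and end dates within the stated months, even accrual: 49% (1 September to 1 February) to 67% (30 September to 28 February).
- Full period with presentation skewed late in the window: 48%; skewed early: 66%; only at 20-27 weeks: 45%.
- Extremes over all combinations tried: about 35% to 78%.

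**Pace.** Entry is possible on 181 − 54 = 127 days at most. Reaching 180 in 127 days instead of 181 needs a daily rate 181 / 127 = 1.43 times as high, while the eligible band is narrowing.

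**Time to due date at entry.** From 14w0d, 182 days = 26 weeks; from 27w6d, 85 days = about 12 weeks.

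**The case against.** The strongest reply is that the two criteria in section 2.2 are compatible with each other, and that February 2019 is only a forecast ("the last woman is expected to be included in the trial in February 2019"). The trial could fill before 5 January. The first part stands: the conflict is between the criteria and the recruitment dates, not within the criteria. But a February inclusion under these criteria is impossible rather than unlikely, and stricter readings of either limit only bring the closing date forward.

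The reply is also right about several stronger conclusions that a reader might draw.

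- *More than half of the pool is lost, as a fact.* The article gives neither an accrual pattern nor the gestation at which women present. The share is conditional on assumptions, and some plausible ones put it below half.
- *The sample as a whole moves to short exposure, about 12 to 17 weeks.* That range fits only entrants from about December. Every woman who can meet both criteria has reached 14 weeks by 30 September. If each entered when first eligible, time to the due date would run from about 12 to 26 weeks and average 20-21 weeks with evenly spread dates. Exposure is short only for those who present late.
- *180 will not be reached and the stated power fails.* No recruitment rate or clinic volume is given, so this cannot be determined.
- *A treatment effect on preterm birth is diluted.* That needs a relation between duration and response that the article does not set out.

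**Conclusion.** The date conflict is established. It needs only the article's own dates and the 280-day convention: under section 2.2 no woman can enter after 5 January 2019 (30 December 2018 on the narrower reading), against an expected last inclusion in February 2019 in sections 2.1 and 3.1. The 54 unusable days out of 181 follow directly, taking enrolment at its widest.

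The pool loss of about 54-57% holds under even accrual from 1 September to 28 February; about 45-67% is a fair range under other plausible assumptions.

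Three consequences are risks only: 180 not reached by the stated dates, eligibility breached late in recruitment, and later entrants confined to late gestation with shorter supplementation. The point must still be settled before recruitment, because the criteria as written cannot be applied over the stated enrolment period.

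**What to change.** Reconcile sections 2.1, 2.2 and 3.1 before the first woman is enrolled. Two routes make the dates agree:

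1. Move the due-date cut-off and the end of follow-up to fit enrolment through February 2019. To keep the whole entry window open to the last day, the cut-off must cover 28 February 2019 + 182 days = 29 August 2019. The cost is an amendment to one eligibility line and the timeline, and about five more months of follow-up (31 March to 29 August is 151 days). Whether the site can support that is not something the article shows.
2. Keep March 2019 and state in sections 2.1 and 3.1 that enrolment closes by 5 January 2019 (30 December 2018 if 27w0d is meant). Then confirm against the site's expected recruitment rate, within the narrowing gestational band, that 180 is attainable, and restate the sample size and power if it is not. The text change is small, but the sample size may have to fall; the attainable number cannot be calculated from the article.

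Under either route, state whether the upper entry limit is 27w0d or 27w6d. Section 3.1 says recruitment had not begun at submission, so either change could be made before any participant is affected.

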### Randomisation and blinding schedule

2.3

Eligible women will be invited to give consent for participation in the trial within 2 weeks of screening. At enrolment, participants will be randomly assigned by a trained research assistant into 2 arms to receive daily oral tablet of 200 μg elemental selenium (arm I) or placebo (arm II) till their delivery using a 1:1 block randomisation code to be generated from Random Allocation software version 1.0 (May 2004) by the study Statistician. The proposed dose of selenium is one-half of the safe and tolerable upper intake level of 400 μg/day for pregnant women.^[18]^ The active drug (selenium) and placebo tablets will be indistinguishable in shape, size, and colour and will be packed in identical coded transparent dispensing sachets by the onsite pharmacy technician who will then store the coded randomization list in a sealed opaque envelope that will be kept in a locked file cabinet at the study site until the end of the study. Twelve (12) dispensing sachets with identical numeric regimen code, containing the same intervention drug will be prepared for each of the participants. At every 2-weekly follow-up visit, a new dispensing sachet with the same numeric code, containing 16 tablets of the same intervention drugs will be given to each woman and pills remaining in used sachets will be counted to assess compliance. In addition, all the women will receive the standard prenatal care (see below). Study investigators and participants will be blinded to the treatment arms until after the final analysis. The onsite pharmacy technician is not involved in the design, conduct, statistical analysis, and reporting of study findings.

### Standard prenatal care

2.4

All the women will receive their routine prenatal care which includes daily doses of ferrous gluconate (300 mg, equivalent to 60 mg of elemental iron) and folic acid (5 mg), and 4-weekly doses of malarial chemoprophylaxis in the form of Sulfadoxine-Pyrimethamine (SP) tablets (from enrolment to 36 weeks of gestation) or instead daily doses of Cotrimoxazole 980 mg for women with CD4 + cell counts < 200 cells/mm^3^ according to established protocol for *Pneumocystis carinii* prophylaxis^[20]^ irrespective of treatment assignments. Alternatively, daily proguanil tablet (100 mg) is given to women with known or recent allergy to Sulphonamides from enrolment to delivery. All women will also be commenced on ART at some point during their follow-up according to the National HIV prevention and treatment guidelines.^[21]^

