### Confirmatory outcome variables

2.6

Primary endpoints – Preterm birth (delivery before 37 completed weeks of pregnancy) and low birth weight in term neonates (baby's birth weight less than 2.5 kg).

Secondary endpoints – HIV disease progression (change in CD4 + cells count, viral load and stage of the disease); mid-trimester miscarriage, change in haemoglobin levels; adverse events (AE) such as hepatotoxicity, gastrointestinal disturbances, dermatologic effects (nail and hair loss and dermatitis), and neurotoxicity; and perinatal mortality (number of stillbirths and neonatal deaths in the first week of life).

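### Women already on ART and women starting it after randomisation appear to be pooled, with neither stratification nor a suitable adjusted model, so the CD4 and viral-load comparison loses precision

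*Protocol article*

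**What the plan says.** Section 2.4 (Standard prenatal care) of the protocol article states that "All women will also be commenced on ART at some point during their follow-up according to the National HIV prevention and treatment guidelines" and gives no fixed time. Section 2.5.1 (Data collection and management) lists "type and duration of ART use (in months" among the enrolment items, next to baseline CD4 count and viral load. The final values are the latest in the case notes, "done within the last 6 weeks of delivery". Section 2.2 opens with "Eligible participants are confirmed HIV-seropositive pregnant women aged 15 to 49 years", and none of its criteria concerns ART.

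Section 2.3 describes allocation "using a 1:1 block randomisation code to be generated from Random Allocation software version 1.0" and names no stratification factor. Section 2.6 lists "HIV disease progression (change in CD4 + cells count, viral load and stage of the disease") as a secondary endpoint. Section 2.7.1 calls its reduction the major secondary endpoint and takes the total of 180 from it.

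Section 2.8 plans independent or paired t tests, or the Mann-Whitney test, for continuous variables. The only adjusted model it names is binary logistic regression, with unnamed confounders.

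**The concern.** Read literally, section 2.4 has every woman starting ART after entry. Section 2.5.1 presupposes that some have used it already, and section 2.1 describes pregnant women with HIV under regular monitoring at the hospital's HIV clinic. Both kinds of women can enter under section 2.2.

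The two kinds should behave very differently on this endpoint. Women who start ART after randomisation should show a large fall in viral load and a rise in CD4 count in either arm. Women already suppressed at entry have little room to change. Pooled raw change then carries a large variance component that has nothing to do with selenium. If that component is left in the error term, a real supplement effect becomes harder to detect.

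There is also a risk of misreading. A before-after test within the selenium arm would count the ART response as a selenium effect.

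**Working it through.** **The plan's own figure.** Section 2.7.1 gives an effect size of 0.3, z values of 1.96 and 1.64, 20% drop-out and a total of 180.

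- One-sample or paired formula: (1.96 + 1.64)² / 0.3² = 12.96 / 0.09 = 144, and 144 / 0.8 = 180. This reproduces the figure exactly.
- Two-arm comparison at the stated 80% power: 2 × (1.96 + 0.8416)² / 0.09 gives 175 per arm, or 350 in total, and 350 / 0.8 gives 438.

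So 180 is a one-sample or paired size. That is a separate fault, but it sets the starting point here. With 90 × 0.8 = 72 evaluable women per arm, two-sided 5%, and d the difference in SD units:

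power ≈ Φ(d × √(72/2) − 1.96) = Φ(6d − 1.96).

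At d = 0.3 this is Φ(−0.16) = 44%.

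**Effect of the mix.** Three inputs are assumptions, because the documents give none of them:

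- p, the share starting ART after entry: 10% to 50%
- D, the extra log10 viral-load fall in starters: 1 to 3
- s, the SD of change within each ART group: 0.5 to 0.7 log10

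The selenium effect is set at 0.3s. Ignoring ART status:

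total SD = √(s² + p(1−p)D²), and d = 0.3s / total SD.

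Example with D = 2, p = 0.3, s = 0.7: variance = 0.49 + 0.21 × 4 = 1.33, SD = 1.15, d = 0.21 / 1.15 = 0.18, power = 19%. ART status accounts for 0.84 / 1.33 = 63% of the variance.

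Power ignoring ART status (range over s = 0.5 to 0.7):

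| D (log10) | p = 10% | p = 30% | p = 50% |
|---|---|---|---|
| 1 | 34–38% | 26–32% | 25–31% |
| 2 | 21–28% | 14–19% | 12–18% |
| 3 | 14–20% | 9–13% | 8–12% |

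The standardised effect falls from 0.30 to between 0.09 and 0.28. With ART status accounted for, the error SD returns to s and power to about 44% in every cell.

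**Bias or precision?** Simulation with D = 2, s = 0.7, 72 per arm, 4,000 trials per row, true effect −0.21:

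| p | Type I error, unadjusted | Mean estimate, unadjusted | Power, unadjusted | Power, adjusted |
|---|---|---|---|---|
| 10% | 4.7% | −0.210 | 28% | 42% |
| 30% | 5.1% | −0.211 | 19% | 45% |
| 50% | 4.4% | −0.211 | 18% | 44% |

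The unadjusted comparison is unbiased and holds its level. What it loses is power.

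**Chance imbalance.** The SD of the arm difference in the share of starters is √(2p(1−p)/72), which is 5.0 points at p = 10% and 8.3 points at p = 50%. The 95% range is about ±10 to ±16 points. This is the same p(1−p)D² term already in the variance above, so it must not be added to the power loss as a second harm.

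**The case against.** A reader might infer that the disease-progression objective cannot be answered, or that the result would be biased by ART. The documents do not support that. The trial is randomised and double-blind, and ART follows national guidelines, so nothing makes its start depend on arm. The between-arm difference estimates the effect of selenium added to ART, and the simulation bears this out. This part of the objection stands in full.

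The size of the loss rests on assumed values. If every woman really starts ART after entry (p = 100%), the mixture loss disappears under this model and simulated power is 43% to 45%, although start times could still vary. The planned Mann-Whitney test would recover part of the loss when starters are few: about 30% power against 17% to 24% for the t test at p = 10%, D = 2 to 3, SD 0.6. At p = 50% it gains little or nothing. CD4 count and stage are not quantified here.

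Section 2.8 does promise control of confounders for secondary outcomes, and the baseline ART data exist. But the model it names is for binary outcomes, so it does not supply the adjustment for continuous change. The absence of stratification rests on what the article describes; the full protocol is not shown and could say more.

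**Conclusion.** The point holds as one of precision and interpretation on the major secondary endpoint. Sections 2.4 and 2.5.1 need reconciling. On the reading that fits both, treated women and later starters are pooled, and the analysis as described leaves ART status in the error term.

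Under the assumed ranges, power for a 0.3 SD effect is about 8% to 38% ignoring ART status and about 44% accounting for it. Power is lower throughout that range, but the amount depends on values the documents do not give. The 44% ceiling comes from the sample-size calculation, and handling ART properly will not lift it to the stated 80%.

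The between-arm comparison remains valid for selenium added to ART. Within-arm change does not isolate a selenium effect. The primary endpoints, preterm birth and low birth weight, are not touched by this point.

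**What to change.** - **Sections 2.4 and 2.5.1:** state consistently whether women enter untreated, treated or both. No change to ART care is implied.
- **Section 2.3:** stratify the block randomisation by ART status at enrolment (on ART / not yet on ART).
- **Section 2.8:** compare end-of-study CD4 count and log10 viral load between arms with one combined linear model (ANCOVA), adjusted for the baseline value and ART status at enrolment. Stratifying without adjusting would not recover the power, because an unadjusted test still carries the full variance. State that before-after change within an arm will not be read as a selenium effect.
- **Sections 2.6 and 2.7.1 and the Discussion:** describe the secondary objective as the effect of selenium added to ART.

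Viral load should stay continuous and the ART groups should stay in one model. Reducing viral load to suppressed or not discards information, and separate tests within ART groups split 72 women per arm into smaller comparisons.

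The cost is two randomisation lists in place of one, one adjusted model and some rewording, with no added visits, tests or women. The article reports that recruitment had not begun at submission, so the lists could be prepared in time. The adjusted model remains available even if they are not.
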